##### Effectiveness

Weekly itemised sales data will be provided annually by each facility to track purchasing behaviours through electronic point-of-sale data. A detailed sales data extraction protocol will guide the procurement of sales data. Data collected will include date of sale, product name, cost and units sold. All available product names derived from sales codes will be matched with products displayed on site (where possible) and also classified for healthiness as ‘GREEN’, ‘AMBER’ or ‘RED’.

### Secondary outcomes

Data collection for secondary outcomes is described in online supplemental appendix IV (Section 3), including monitoring nutritional profile of available food and drinks, healthiness of the in-store food environment, resource use surveys to inform the cost-effectiveness of the support package and process evaluation measures including retailers’ practices and perceptions, relevant parties’ perceptions, customer satisfaction survey, LG policy progress, as well as contextual and reach data. Covariates for consideration are also outlined.

### Statistical methods

#### Primary outcomes

*Implementation*: Initially, the effect of Promoting CHANGE on each outcome will be assessed at the 3-year mark, using a GEE model^36^ to account for clustering within LGs, adjusted for facility characteristics. The GEE model framework will also be used to assess the effect of Promoting CHANGE on the six monthly outcomes over time.

*Effectiveness*: The effect of the intervention on the rate of change of weekly sales over the 3-year trial will be assessed using a GEE framework to account for autocorrelation in weekly trends over time. The model will include intervention, time and their interaction; facility as a fixed effect; and will adjust for weekly temperature and facility characteristics. Sensitivity analyses will also help handle any missing data. All analyses will be performed on an intention-to-treat basis, for all randomised participants for which there are available data.

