### Sample size considerations

Power calculations for sample size were performed in PASS (V.16). They were based on the number of LGs recruited and the number of non-seasonal facilities that agreed to provide display and point-of-sale data used to evaluate the sales outcomes. This included 21 non-seasonal facilities in four LGs in the Intervention group and 14 facilities in four LGs in the Control group (mean n=5 and n=4 sites per LG, respectively). *Primary implementation outcome*: The trial will have 80% power to detect a mean difference between groups of ≥18.8% in the percentage of ‘RED’ drinks displayed at the end of the 3-year trial (intraclass correlation coefficient 0.05, cluster size variation coefficient 0.37, SD=17.8, α=0.05, 2-sided test).^16 30^ This effect size is similar to that observed in the Water in Sport project—an uncontrolled pre-post natural experiment conducted in sports and recreation settings in Victoria, Australia (−18.9% at 18 months).^16 30^
*Primary effectiveness outcome*: With 156 weeks of sales data, the trial will have 80% power to detect a difference of ≥9% between groups in the percentage of ‘RED’ drink weekly drink sales at the end of the 3 year trial, using a generalised estimating equation (GEE) model assuming linear trends^36^ (first-order autoregressive, AR(1) correlation structure, ρ=0.73, SD=13.7). This effect size is smaller than in Water in Sport (−11% at 2 years).^30^ As of December 2024, due to the drop-out of one recruited LG and the withdrawal of some individual facilities in other LGs, the trial involves three LGs in the Intervention group, with a total of 16 non-seasonal facilities, and four LGs in the Control group, with a total of 8 non-seasonal facilities.

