### Data collection

Data collection will be conducted by project officers in Intervention LGs and nominated data collectors in Control LGs, who will receive annual training by the research team and HEAS to enhance the rigour of their data collection practices. The research team will also collect data independently at T0 and T6, to ensure objectivity of results for overall trial evaluation. This will also ensure that any final changes implemented within the intervention group, between T5 and trial end, will be captured.

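### The 3-year model for the primary display outcome does not name each facility's baseline (T0) RED percentage as a covariate, although T0 is measured; the plan should say that it is included.

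*Protocol article*

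**What the plan says.** Under Statistical methods, Primary outcomes (Implementation), the Protocol article states that "the effect of Promoting CHANGE on each outcome will be assessed at the 3-year mark". The stated method is a GEE, fitted "to account for clustering within LGs, adjusted for facility characteristics". It then adds a longitudinal analysis: "The GEE model framework will also be used to assess the effect of Promoting CHANGE on the six monthly outcomes over time". Facility characteristics are not defined, and T0 RED percentage is not mentioned for either analysis.

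The baseline value will exist. Photo audits run every six months, and under Data collection "The research team will also collect data independently at T0 and T6". FoodChecker assessments from both groups are to be cross-checked at T0 and T6.

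The sales model in the same section is treated differently: "The model will include intervention, time and their interaction; facility as a fixed effect".

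Sample size considerations gives "80% power to detect a mean difference between groups of ≥18.8% in the percentage of ‘RED’ drinks displayed at the end of the 3-year trial", with SD 17.8, ICC 0.05 and a cluster size variation coefficient of 0.37. No baseline correlation is given. Randomisation and blinding lists the pairing factors as location, socioeconomic index and number of engaged facilities.

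On covariates, the Secondary outcomes part of Data collection refers to online supplemental appendix IV, which is not shown: "Covariates for consideration are also outlined".

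**The concern.** The first display analysis has a stated time point, model, clustering level and type of adjustment. It does not name the covariate most likely to matter, which is the same facility's RED percentage before the intervention. Three features of the text suggest a plain end-of-trial comparison:

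- The facility fixed effect in the sales model absorbs each facility's own level. The display model has no counterpart.
- The power figure can be reproduced from the raw SD with no baseline term (see the working).
- The pairing did not use RED percentage, so the design does not balance it directly.

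Two things are at stake. One is precision, in a trial now smaller than its power calculation assumed. The other is interpretation. If the arms differ at T0, the part of that gap which persists to T6 sits inside the estimated effect, and with 24 facilities in 7 LGs such a gap could be sizeable.

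**Working it through.** **Inputs from the Protocol article.** SD 17.8, ICC 0.05, cluster size variation coefficient (CV) 0.37, two-sided alpha 0.05, 80% power. Planned: 21 facilities in 4 LGs against 14 in 4 LGs. As of December 2024: 16 in 3 LGs against 8 in 4 LGs.

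**Assumptions.** The SD and ICC, stated for RED drinks displayed at the end of the trial, also hold at T0 and for food and drinks together. The CV stays at 0.37 after the losses. The T0 to T6 correlation r is not in the documents and is taken from 0.3 to 0.7. Adjustment leaves the ICC unchanged.

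**Formula.** For an arm with K LGs and a mean of m facilities per LG, DEFF = 1 + ((CV² + 1)m - 1) × ICC and variance = SD² × DEFF / (K × m). SE is the square root of the sum over arms. The detectable difference is (1.960 + 0.842) × SE.

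**1. The plan's figure.**
- Intervention, m = 5.25: DEFF 1.248, variance 316.84 × 1.248 / 21 = 18.84.
- Control, m = 3.5: DEFF 1.149, variance 316.84 × 1.149 / 14 = 26.00.
- SE = sqrt(44.84) = 6.70. Detectable difference 18.76, against the stated 18.8. Power at 18.8 is 80.2%.

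The stated figure is therefore reproduced with no baseline term.

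**2. The current sample.**
- Intervention, m = 5.33: DEFF 1.253, variance 24.82.
- Control, m = 2: DEFF 1.064, variance 42.13.
- SE = sqrt(66.94) = 8.18. Detectable difference 22.9. Power at 18.8 is 63%.

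**3. Chance difference at T0.** The same SE, 8.18, is the standard deviation of the T0 difference between arms. The probability of a gap above 10 points in either direction is 2 × (1 - Φ(10 / 8.18)) = 0.22. With equal SDs at the two times, about r times a T0 gap carries into the unadjusted T6 contrast. For a 10-point gap that is 3 to 7 points at r = 0.3 to 0.7.

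**4. Effect of adjustment, current sample.** SE becomes 8.18 × sqrt(1 - r²). The t columns use LG-level degrees of freedom: 7 - 2 = 5 unadjusted, and 4 if the covariate costs one.

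| r | SE | Detectable, normal | Power at 18.8, normal | Detectable, t | Power at 18.8, t |
|---|---|---|---|---|---|
| unadjusted | 8.18 | 22.9 | 63% | 28.8 (5 df) | 46% |
| 0.3 | 7.81 | 21.9 | 67% | 29.4 (4 df) | 45% |
| 0.5 | 7.09 | 19.9 | 76% | 26.7 (4 df) | 52% |
| 0.7 | 5.84 | 16.4 | 90% | 22.0 (4 df) | 68% |

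The t columns are one bound. T0 varies between facilities within an LG, so its cost may fall partly at facility level and be less than a full LG-level degree of freedom.

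**The case against.** **The text does not say that baseline is left out.** T0 RED percentage could be one of the undefined facility characteristics, and covariates are outlined in an appendix that is not shown. A reader might infer that the outcome is compared without any baseline adjustment. The documents do not support that. What can be said is that the model as written does not name T0. The appendix pointer does not settle the matter either, because it stands under Secondary outcomes and speaks only of covariates for consideration.

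**The longitudinal GEE may deal with it.** If T0 is in the six-monthly model, baseline differences could be accounted for there. This is possible, so it cannot be said that imbalance goes uncorrected. However, the article does not say how T0 enters that model, and the 3-year comparison comes first.

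**Chance imbalance is not bias.** This stands. Over repeated randomisations the unadjusted contrast is unbiased, and the 8.2 points are already part of its standard error. Reading them as an added error would count them twice. The argument for adjustment is conditional: once a T0 gap has been observed in this trial, the unadjusted estimate carries part of it. The calculation also ignores the pairing, which may reduce the gap somewhat.

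**The gain depends on an unknown correlation and on the reference distribution.** This also stands. A three-year programme meant to change what is stocked could weaken r. With LG-level t inference there is no gain at about r = 0.3.

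**Conclusion.** The point holds as a matter of specification. The primary display model is an end-of-trial comparison that names facility characteristics and not the T0 value of the outcome, although T0 is measured in both arms and was not a pairing factor. In the current sample a chance T0 gap has an SD of about 8.2 points, against a target of 18.8.

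The precision benefit ranges from none, at r near 0.3 with LG-level t inference, to a detectable difference of 16.4 instead of 22.9 at r = 0.7 on the normal approximation. At r = 0.5 there is a gain on both bases: 22.9 to 19.9, and 28.8 to 26.7. All of this rests on an assumed r and on the plan's SD and ICC applying at T0.

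A reader might also take this as evidence that the stated 18.8 is wrong. It is not: that figure is reproduced for the planned sample without a baseline term.

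**What to change.** State that each facility's T0 RED percentage is a covariate in the 3-year display model, or model T0 and T6 jointly with a group-by-time term. State also how T0 enters the six-monthly GEE, as a covariate or as one of the outcomes. The other facility covariates need not be dropped to make room for it. If appendix IV or the analysis plan already lists T0 RED percentage, a sentence saying so for the primary display model is enough.

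The cost is wording, since T0 collection is already planned and evaluation is scheduled for mid 2026 to 2027. The price in the analysis is up to one degree of freedom, which matters with 7 LGs, and a simple rule fixed in advance for any facility without a T0 audit.

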**Methods and analysis:**

A 3-year, type 2 effectiveness-implementation hybrid cluster randomised controlled trial will evaluate the Promoting CHANGE capacity-building and support package in three Intervention and four Control LGs in Victoria, Australia (August 2023–July 2026). The co-designed initiative includes human resource support, training, tools, technical assistance, community-of-practice groups, feedback based on food outlet audit and sales data and small grant incentives. Using the RE-AIM (Reach, Effectiveness, Adoption, Implementation, Maintenance) evaluation framework, the trial’s co-primary outcomes are the percentage of least healthiest food and drinks (1) displayed (implementation) and (2) sold weekly (effectiveness). Key secondary outcomes are effectiveness (sales and revenue); facility-level adoption, implementation, maintenance of healthy changes; cost-effectiveness (within-trial modelled economic evaluation). Findings will provide evidence of the initiative’s effectiveness and scalability, informing recommendations for advancing healthier food environments in over 6000 community-based food outlets across 500 Australian LGs, with implications globally.

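### The display outcome is analysed by GEE with only seven LGs as clusters; the standard test would reject a true null about 15-16% of the time or more, and the power figure ignores the LG count

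*Protocol article*

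**What the plan says.** Under Statistical methods, Primary outcomes, the implementation outcome is assessed at 3 years by a GEE "to account for clustering within LGs, adjusted for facility characteristics", and the same framework is used for the six-monthly audits. Randomisation and blinding makes the LG the randomised unit, allocated within four pairs, and reports that one of the eight LGs left after randomisation.

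Sample size considerations plans on "21 non-seasonal facilities in four LGs in the Intervention group and 14 facilities in four LGs in the Control group" and claims 80% power for a difference of 18.8 percentage points, using "intraclass correlation coefficient 0.05, cluster size variation coefficient 0.37, SD=17.8, α=0.05, 2-sided test". The same section then reports that "the trial involves three LGs in the Intervention group, with a total of 16 non-seasonal facilities". On the other side, all four Control LGs remain but only 8 facilities are left among them. It gives no revised detectable difference or power after that. The article names no variance estimator, reference distribution or small-sample correction for the GEE.

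**The concern.** The GEE sandwich variance is justified by a large number of independent clusters. With few clusters it is biased downwards, and a normal reference ignores how poorly it is estimated. Here there are seven clusters, with a mean of 16/3 = 5.3 facilities per Intervention LG and 8/4 = 2 per Control LG, and facility covariates are added. Run in its ordinary form, the named method would not hold its 5% error rate, and its 95% intervals would cover about 84% in the near-even case (100 - 16).

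The power statement points the same way. It is the one place where the article shows its inference for this outcome, and it does not appear to use degrees of freedom based on the number of LGs. At stake are the credibility of a co-primary claim and a realistic view of what the trial can detect.

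**Working it through.** **1. The plan's own figure.** Inputs from Sample size considerations: 21 and 14 facilities in 4 and 4 LGs (m = 21/4 = 5.25 and 14/4 = 3.5), ICC 0.05, CV 0.37, SD 17.8, two-sided 5%, 80% power.

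Design effect: DE = 1 + [(CV² + 1)m - 1] × ICC.
- Intervention: 1 + (1.1369 × 5.25 - 1) × 0.05 = 1.248
- Control: 1 + (1.1369 × 3.5 - 1) × 0.05 = 1.149

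SE = 17.8 × √(1.248/21 + 1.149/14) = 6.696. With a normal reference the detectable difference is (1.960 + 0.842) × 6.696 = 18.76, and power at 18.8 is 80.2%. The stated 18.8 reproduces. Facility-level degrees of freedom with the rounded means of 5 and 4 per LG come close as well (18.6 to 18.9), so the two cannot be told apart.

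**2. The same design on LG-level degrees of freedom.** Eight LGs minus 2 gives 6. With the same SE and a t test, power at 18.8 is 65% and the detectable difference is about 22.5. Varying the rounding of m and the use of the CV gives 21.8 to 22.7, so 18.8 is not reached on this basis.

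**3. The LGs now in the trial.** With 16 facilities in 3 LGs and 8 in 4, the design effects are 1.253 and 1.064, and SE = 17.8 × √(1.253/16 + 1.064/8) = 8.182. On 7 - 2 = 5 degrees of freedom, power at 18.8 is about 46% and the detectable difference about 28.8 (28.5 without the CV term).

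**4. Type I error of the GEE test.** Data were simulated with no treatment effect, identity link, LG as cluster, 3 vs 4 LGs, 16 vs 8 facilities and ICC 0.05, using 4,000 to 40,000 datasets per setting in several independent runs. The uncorrected variance is A⁻¹(Σ Xₖ′eₖeₖ′Xₖ)A⁻¹ with A = X′X, shown for independence working correlation. Mancl-DeRouen replaces eₖ by (I - Hₖ)⁻¹eₖ, and Kauermann-Carroll uses the power -1/2. Facilities per LG are assumed, since only the totals are given. Rejection rates at nominal 5%:

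| Assumed facilities per LG | Uncorrected, z | Kauermann-Carroll, t(5) | Mancl-DeRouen, t(5) | t-test on LG means |
|---|---|---|---|---|
| 5,5,6 vs 2,2,2,2 | 14.8-16.7%, mostly 15-16% | 4.9-5.4% | 2.8-3.3% | 4.3-4.9% |
| 4,5,7 vs 1,2,2,3 | 16.5-16.8% | 5.3% | 2.9-3.0% | 4.2% |
| 3,5,8 vs 1,2,2,3 | 16.7-17.4% | 5.5% | 2.9-3.0% | 4.2% |
| 3,5,8 vs 1,1,2,4 | 19-19.5% independence; 24-25% exchangeable | 6.7% independence; 8.6-10% exchangeable | up to 4.0% | 4.0% |

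- One to three facility covariates raise the uncorrected rate to about 17-20% in the first and third splits.
- With the first split, ICC values from 0 to 0.20 leave the uncorrected rate at 15.8-16.0%.
- Keeping the uncorrected variance but using t(5) still gives 8-9% in the first three splits.
- The planned 4 vs 4 LGs would already have given 14.3-14.7%, so the problem did not begin with the lost LG.
- Rejections in favour of the intervention alone were 7.5-8.5% with the first split and 10-13% with the most uneven one, against a nominal 2.5%.

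**The case against.** The strongest reply is that this rests on silence. A condensed article commonly leaves the variance estimator and reference distribution to the analysis plan, which is not shown. A GEE with a corrected variance and a t reference is fully compatible with the text. That stands, and it is why the error rates above are conditional on the standard test. It does not dispose of the point, because the ordinary form of the named method has the wrong error rate at this number of LGs, and the printed power figure does not reproduce on LG-level degrees of freedom.

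Two further limits stand. Current facilities per LG are unknown, so the uneven splits illustrate a range. The simulation and the 5 degrees of freedom also ignore the pairing described under Randomisation and blinding.

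A reader might infer that a permutation test is ruled out because seven LGs allow too few arrangements. The documents do not support that as a simple count. Unrestricted 3 vs 4 allocation has 35 arrangements, and a test on the absolute difference can reach 1/35 = 0.029. Allocation was in fact within pairs, at most 2⁴ = 16 arrangements, so 35 is not this trial's reference set. Nor does anything here establish a particular limit on the number of covariates.

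**Conclusion.** The point holds in conditional form. If the standard GEE test is applied to the display outcome, its two-sided type I error is about 15-16% with near-even LG sizes and roughly 17-25% with uneven sizes or facility covariates. This rests on seven LGs contributing data, the assumed splits, ICC 0.05 and analysis without the pairing. The power finding does not depend on the splits: 18.8 points at 80% power takes no account of the number of LGs, and on 6 degrees of freedom the planned design had about 65% power at that difference.

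Two stronger readings are tempting. One is that the trial will use an uncorrected test; the article neither says so nor excludes it. The other is that a false claim of benefit is likely; about 8% of null trials would reject in the intervention's favour with near-even sizes, which is about three times the nominal 2.5% but far from likely. The effectiveness model is specified differently and was not simulated, so these error rates do not carry over to it.

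**What to change.** State before analysis that LG-clustered models use a Mancl-DeRouen bias-corrected variance with a t reference on the number of LGs minus 2 (5 degrees of freedom). Kauermann-Carroll would do only if LG sizes turn out near even. Give a comparison of LG means as a supporting analysis. Restate the detectable difference or power on LG-level degrees of freedom for the three and four LGs now in the trial. If the analysis plan already does this, a sentence saying so is enough.

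The change is one software option and a few sentences. The price is wider intervals and a less favourable power figure: simulated power at 18.8 points is about 35% with Mancl-DeRouen, 49% with Kauermann-Carroll and 44% with LG means (near-even split).

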### Randomisation and blinding

Eight LGs were paired based on location (regional/urban), the socioeconomic index for areas,^37^ and the number of engaged facilities. At the end of September 2021, a statistician independent of the project produced the restricted random sequence to allocate LGs to Intervention or Control within pairs. The nature of the intervention precludes concealing LG allocation, as participants were informed of their grouping by the project lead. Data collectors, who are employees of the participating LGs, will not be blinded to intervention allocation. The study statistician will be blinded during analysis. After randomisation, one LG dropped out prior to the start of the trial in October 2022, citing altered LG capacity to participate.

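### The sales model and its power statement name no LG-level clustering, although LGs were randomised; if trends correlate within LGs, standard errors are too small and power is overstated

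*Protocol article*

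**What the plan says.** Randomisation was at LG level. Under Randomisation and blinding, an independent statistician "produced the restricted random sequence to allocate LGs to Intervention or Control within pairs".

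Statistical methods, Primary outcomes, treats the two co-primary outcomes differently. The display (implementation) model is a GEE that is said to account for clustering within LGs. The sales (effectiveness) model assesses the rate of change of weekly sales "using a GEE framework to account for autocorrelation in weekly trends over time". Of its terms the article says: "The model will include intervention, time and their interaction; facility as a fixed effect". Weekly temperature and facility characteristics are the adjustments. No LG cluster, LG random effect or LG-by-time term is named for sales.

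Sample size considerations shows the same split. The planned size is "21 non-seasonal facilities in four LGs in the Intervention group and 14 facilities in four LGs in the Control group". For display, an ICC of 0.05 and a cluster-size coefficient of variation of 0.37 are listed. For sales: "With 156 weeks of sales data, the trial will have 80% power to detect a difference of ≥9% between groups", from a "generalised estimating equation (GEE) model assuming linear trends" with "first-order autoregressive, AR(1) correlation structure", ρ = 0.73 and SD 13.7. No ICC is listed. The same section gives the December 2024 position as 16 facilities in three Intervention LGs and 8 in four Control LGs.

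**The concern.** A facility fixed effect absorbs constant differences between facilities, and so between LGs. It does not absorb LG-specific trends. The tested term is the intervention-by-time interaction, so variation between LGs in trend belongs in its error. A model that handles only week-to-week correlation within a facility leaves that variation out.

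The article gives reasons to expect some shared trend. Study setting says that LG policy mandates and funding changes could affect facility outcomes. Human resource support places project officers at LG level and ties product choice to local suppliers. Study design allows other initiatives in both groups.

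At stake are the type I error and interval width of a co-primary test that rests on seven remaining randomised units, and a power figure that may be too favourable even at the planned size.

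**Working it through.** **Inputs from Sample size considerations.** Sales: 156 weekly points, ρ = 0.73, SD 13.7, 21 vs 14 facilities. Display: ICC 0.05, CV 0.37, SD 17.8, two-sided α = 0.05. I assume the same α and sidedness for sales.

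**1. Reproduce the sales figure with independent facilities.** The variance of one facility's estimated 3-year change (slope × 155 weeks) under AR(1) errors is 85.8 with an independence working correlation (SD 9.27) and 82.5 with an AR(1) working correlation (SD 9.08).

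SE = √[variance × (1/21 + 1/14)], and the minimum detectable difference (MDD) is (1.960 + 0.842) × SE.
- Independence working: SE 3.20, MDD 8.96 points, power at 9 points 80.4%.
- AR(1) working: SE 3.13, MDD 8.78, power 81.9%.

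The stated 9 points at 80% is reproduced with no LG clustering.

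**2. Cross-check on display.** Design effect per arm = 1 + [(CV² + 1)m − 1] × ICC, with m = 21/4 = 5.25 and 14/4 = 3.5. At ICC 0.05 this gives 1.248 and 1.149.

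MDD = 2.802 × 17.8 × √(1.248/21 + 1.149/14) = 18.76, against 18.8 stated. Without the ICC it would be 17.2. LG clustering was therefore included for display.

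**3. Add LG clustering to sales at planned size.** The article gives no ICC for sales trends, so this is a range of assumptions, using the same formula and CV. The SE ratio is the clustered SE over the unclustered SE. Type I error is 2 × [1 − Φ(1.96 / ratio)], for a normal-based test that uses the unclustered SE. Ranges cover the two working correlations.

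| Trend ICC | SE ratio | Type I error | MDD (z) | Power at 9 (z) | Power at 9 (t, 6 df) |
|---|---|---|---|---|---|
| 0 | 1.00 | 5.0% | 8.8–9.0 | 80–82% | 65–67% |
| 0.01 | 1.02 | 5.4% | 8.9–9.1 | 79–81% | 64–65% |
| 0.05 | 1.09 | 7.2% | 9.6–9.8 | 73–75% | 58–60% |
| 0.10 | 1.17 | 9.5% | 10.3–10.5 | 67–69% | 52–54% |
| 0.20 | 1.33 | 13.9% | 11.6–11.9 | 57–58% | 43–44% |

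The last column has its own starting point. Moving from z to 6 df already lowers power to 65–67% at ICC 0, so only the fall below that comes from clustering.

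**4. Current size (16 vs 8 facilities, 3 vs 4 LGs).** With no LG clustering, power at 9 points is 61–63% and the MDD is 11.0–11.2. At ICC 0.05, power is 56–58% (z) or 40–42% (t, 5 df), and the MDD is 11.7–11.9 (z). Most of the z-based fall from 80% is lost facilities; clustering takes about a further 5 points.

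**The case against.** The strongest reply is that the article does not say what the GEE cluster is for sales. A GEE clustered on the LG with a robust variance, plus facility fixed effects, fits its wording and would cover correlated trends. A condensed article may leave that to an analysis plan. This stands as far as it goes: a reader might infer that the analysis definitely ignores the LG and that its standard errors are certainly too small, and the text does not support that certainty. The reply does not clear the point. The article names LG clustering for one co-primary outcome and a different correlation target for the other, and a robust variance on seven clusters would still need a small-sample correction.

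Three further limits stand.
- **Reproduction.** A reader might infer that 9 points can be obtained only with 35 independent facilities. With an AR(1) working correlation, ICC 0.01 gives 8.94 points (80.5% power at 9) and ICC 0.015 gives 9.02 (79.8%). The arithmetic cannot separate zero from about 0.01. The evidence for omission is mainly that no ICC is listed.
- **Larger type I errors.** Facility-clustered sandwich errors with a normal reference give about 10% in simulation at 16 vs 8 and ICC 0.05 (LG sizes 5, 5, 6 and 2, 2, 2, 2 assumed). The same method gives 8.3% at ICC 0, so 3.3 of the 5.0 excess points are small-sample sandwich bias, a separate matter.
- **The ICC itself.** The 0.05 is for a displayed level, not a sales trend. A common value in both arms is also an assumption, because project officers exist only in the Intervention group and lease arrangements vary by governance model.

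**Conclusion.** The concern holds in conditional form. As written, the sales model and its power statement name no LG-level clustering, although the LG is the randomised unit and display has it in both places. Facility fixed effects do not close the gap, because the tested term is a trend.

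The direction of the error rests on positive within-LG correlation of trends, and its size on an ICC that the article does not give. At 0.01 the effect is slight; at 0.05 to 0.20 it is material for a co-primary test. The power statement should not be relied on for this outcome unless the LG-level correlation is negligible and the original 35 facilities are retained, and the second condition has already failed.

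**What to change.** In Statistical methods, name the LG as the cluster for the sales model, with a small-sample correction and LG-based degrees of freedom. Alternatively, estimate each facility's slope, summarise to the LG, and compare three with four LG values against a t reference on 5 df. Either is preferable to a model with random intercepts and slopes at both LG and facility level, which is more than seven LGs are likely to support. Say how the pairing is handled now that one LG has left.

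In Sample size considerations, restate the sales power or detectable difference over a range of LG ICCs (for example 0.01 to 0.20), for the planned and the current numbers.

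The cost is wording and a recalculation, with no new data. Confidence intervals will be wider and stated power lower. Evaluation is planned for mid 2026–2027, so the change can precede the analysis.
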